### Secondary objectives

To compare the effect of the FIT-HIP intervention with usual care with respect to improving the degree of independence in ADL (Barthel index), ambulation ability (Functional Ambulation Categories) and walking speed.To compare the number of fall incidents, mortality, hospital (re)admission and psychosocial functioning (social participation after discharge from GR, measured by the Utrecht Scale for Evaluation of Rehabilitation-subscale Participation; and quality of life, measured by the EuroQol 5D) between the FIT-HIP intervention and usual care.To examine the feasibility of the FIT-HIP intervention for participants and therapists conducting the FIT-HIP intervention.To perform an economic evaluation, consisting of a cost analysis and cost-utility analysis, comparing the FIT-HIP intervention with usual care. Costs will be measured from a healthcare perspective.

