#### Additional variables

Table 2 gives an overview of the additional variables assessed in this trial.

**Table 2 Tab2:** Additional variables assessed in the FIT-HIP trial

Domain	Assessment	Description	Time point(s)
Socio-demographics	Age, gender, marital status, type of residence prior to hip fracture		BA
General health and physical functioning	Functional comorbidity index (weighed) [46]	Assesses 18 comorbid conditions and their effect on physical functioning.	BA
	Medication use	Number and type of medication used by participants. Assessed by ECP (questionnaire).	BA, DA
	Assistive walking device	Type of assistive walking aid, used for indoor and outdoor usage. Assessed by questionnaire.	BA
	Use of formal care (home care) and informal care (given by relatives/volunteers)	Assessed by questionnaire.	BA, FU1, FU2
	Previous fall frequency	Number of falls in 6 months prior to hip fracture.	BA
	Handheld grip strength	Evaluated with dynamometer.	BA
	Nutritional status: Body Mass Index	Calculated by dividing bodyweight in kilograms by length in meters squared.	BA, DA
	Numeric Pain Rating Scale (NPRS) [47]	Assesses intensity of pain on an 11-point scale (0 –10).	BA, DA, FU1, FU2
Hip fracture (related) characteristics	Type of fracture, operation, weight-bearing capacity	Assessed by ECP (questionnaire).	BA
	Duration of hospital admission due to hip fracture	Number of days in hospital.	BA
	Complications during hospital admission due to hip fracture	Number and type of complications. Assessed by ECP (questionnaire).	BA
Neuropsychological factors	Mini Mental State Examination (MMSE) [48, 49]	Screens for cognitive disorders and dementia	BA
	Geriatric Depression Scale, 8-item (GDS-8) [50]	Short adapted version of the GDS-30. Developed to screen depression in nursing home population.	BA
	Hospital anxiety and depression scale – subscale anxiety (HADS-A) [51]	Screens for anxiety.	BA
	Utrecht Coping List; subscales active and passive coping. (UCL) [52]	Assesses coping mechanism. Questionnaire assesses how a person deals with problematic situations in general.	BA
	Pittsburgh Rehabilitation Participation Scale [53]	Participation/motivation for physiotherapy (PT) during GR.	During every session of PT until discharge

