### Economic evaluation

The economic evaluation consists of a cost analysis and a cost-utility analysis, both with a 6-month time horizon after discharge from GR. Costs will be measured from a healthcare perspective. In the cost-utility analysis, the difference in healthcare costs between the strategies will be compared to the difference in Quality-Adjusted Life Years (QALYs, calculated using the 3-level Dutch EQ-5D tariff [38] and the visual analogue scale for health). Estimated healthcare costs will include the costs of the FIT-HIP intervention (estimated from the study registration) and other healthcare utilisation (estimated using quarterly questionnaires filled in by the patients). Other healthcare utilisation will include care provided by general practitioners, consultations of medical specialists and paramedics, home care, informal care, hospitalisation, and residential care. A cost-price analysis will be performed for the FIT-HIP intervention; other healthcare items will be valued using standard prices.

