### Data analyses

Differences between the intervention and control group in characteristics of participants at baseline will be tested with chi-square tests for categorical variables, Mann-Whitney *U*-test for continuous variables with skewed distributions, and one-way ANOVA for normally distributed continuous variables. Given the hierarchical data structure, multilevel analyses will be used for continuous outcomes, and logistic Generalized Estimated Equation (GEE) analyses for dichotomous outcomes. Logistic GEE is preferred to logistic multilevel analyses because of the instability of the latter. Analyses will be based on an intention-to-treat principle and the level of significance will be set at *p* < 0.05. Missing data will be handled as missing (no imputation). Multilevel analyses will be performed with MLwiN. All other analyses will be performed with IBM SPSS statistics.

With regard to the qualitative data (assessed for the process evaluation), these will be analysed by means of coding techniques based on transcriptions of the qualitative interviews. In the economic evaluation, group averages will be compared using unequal-variance t-tests, according to the intention-to-treat principle. Costs will be compared to QALYs using net-benefit analysis. Multiple imputation will be used to account for missing values. Sensitivity analysis will be performed on the time horizon (base case 6 months vs. 12 months) and the utility measure (base case Dutch EQ-5D tariff vs. visual analogue scale for health).

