## Discussion

At present, the functional recovery after a hip fracture in frail older adults is limited, resulting in a considerable amount of long-term disability. Therefore, a hip fracture has major consequences for individual patients, as well as for society, due to the costs of healthcare and the burden on caregivers. Based on the current literature, only a few factors influencing functional recovery after hip fracture could prove to be modifiable. As fear of falling is highly prevalent in hip fracture patients and leads to avoidance of activity, it is probably a significant factor contributing to limited recovery after hip fracture. To our knowledge this is the first RCT to evaluate the effect of treatment of fear of falling in this population. This multicentre cluster RCT will provide insight into whether targeted treatment of fear of falling during geriatric rehabilitation after hip fracture, using the FIT-HIP intervention, is effective in reducing fear of falling and associated avoidance of activities and, therefore, improving functional outcome after hip fracture.

The key component in this trial, guided exposure, is based on the principles of cognitive behavioural therapy. It encourages the systematic confrontation of feared stimuli (situations), in a graded approach. It is the preferred treatment in various types of anxiety disorders, including phobias. In the FIT-HIP programme, the guided exposure is used in conjunction with psycho-education and cognitive restructuring. The programme has been developed together with experts that developed a treatment programme on fear of falling in community-dwelling older adults, which was shown to effectively reduce the fear of falling [21–26].

Because the FIT-HIP programme is integrated in usual care, the additional costs are expected to be limited. In an earlier phase we conducted a small pilot study, aimed at testing the FIT-HIP training and the feasibility of the intervention for healthcare professionals and participants. The additional time spent on therapy for the purpose of this intervention appeared to be limited in the pilot, but will become clear after the evaluation of the intervention. Also, guided exposure was easily integrated in the usual care. Although the principles of guided exposure are often practiced in usual care, they are not generally as structured and intentional as in this intervention.

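### The economic evaluation states a healthcare perspective but prices informal care as healthcare use, so its cost difference and net benefit are not the quantities the objective names

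*Protocol article*

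**What the plan says.** **Perspective.** The last of the Secondary objectives in the protocol article calls for a cost analysis and a cost-utility analysis and says: "Costs will be measured from a healthcare perspective". The Economic evaluation section repeats the sentence and defines the contrast of interest accordingly: "the difference in healthcare costs between the strategies will be compared to the difference in Quality-Adjusted Life Years".

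**Items counted.** The same section then builds the cost total from the cost of the intervention plus other healthcare use reported by patients in questionnaires. The list of that other use ends with "home care, informal care, hospitalisation, and residential care". On valuation it says that "other healthcare items will be valued using standard prices", so informal care enters the total with a price.

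**What informal care means here.** Table 2 (Additional variables) has a row for "Use of formal care (home care) and informal care (given by relatives/volunteers"), collected at baseline and at both follow-ups.

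**How the total is used.** Under Data analyses, group averages in the economic evaluation are compared with unequal-variance t-tests, and "Costs will be compared to QALYs using net-benefit analysis". Two sensitivity analyses are named, one on the time horizon and one on the utility measure. Neither concerns the perspective or informal care.

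**The concern.** A costing perspective says whose costs are counted. The article names the healthcare perspective twice and then counts help from relatives and volunteers as healthcare. The reported difference in healthcare costs would contain something other than healthcare costs, and the net benefit would inherit it.

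This could matter because the trial's rationale, given in the Background, is that treating fear of falling leads to better recovery and more independence. If that happens, the help participants need from family may change, so equal informal care in the two arms cannot simply be assumed. If informal care fell in the intervention arm, the trial would report as a healthcare saving an amount that the healthcare system does not receive. If it rose, the trial would report a healthcare cost that the system does not bear. No planned analysis would let a reader separate the two parts.

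**Working it through.** The plan states no figure for this item, so there is none to reproduce. The check is a comparison of the text followed by simple algebra.

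**Step 1: the texts side by side**

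| Place in the protocol article | What it fixes |
|---|---|
| Secondary objectives | Healthcare perspective |
| Economic evaluation, perspective sentence | Healthcare perspective |
| Economic evaluation, contrast | Difference in healthcare costs against difference in QALYs |
| Economic evaluation, item list | Informal care counted as healthcare use, separately from home care |
| Economic evaluation, valuation | Items priced at standard prices |
| Table 2 | Informal care is given by relatives or volunteers; formal care is home care |
| Data analyses | No sensitivity analysis on perspective or on informal care |

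Home care and informal care are separate entries in the item list, and Table 2 separates them again, so informal care cannot be read as paid home care under another name. The Discussion also names two distinct burdens: "due to the costs of healthcare and the burden on caregivers". No section widens the perspective or defines healthcare so as to include unpaid help.

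**Step 2: effect on the planned results**

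Let Δ denote intervention minus control and λ the value placed on one QALY.

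- Cost difference as planned: ΔC = ΔC_healthcare + ΔC_informal
- Net benefit as planned: NB = λ × ΔQALY − ΔC = (λ × ΔQALY − ΔC_healthcare) − ΔC_informal

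The bracket is the healthcare-perspective net benefit. The planned net benefit differs from it by −ΔC_informal at every value of λ. The gap is zero only if mean informal-care cost is the same in both arms.

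Precision changes too. Within an arm, the variance of the total is Var(C_healthcare) + Var(C_informal) + 2 × Cov(C_healthcare, C_informal), and this feeds the planned t-test. The article does not allow the size or direction of that change to be stated.

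**Step 3: illustration on assumed inputs**

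From the article: a 6-month horizon after discharge, taken as 26 weeks. Assumed, because the article gives neither: a between-arm difference of 1 hour of informal care per week, and a price of 10 to 20 euros per hour.

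- Lower end: 1 × 26 × 10 = 260 euros per participant
- Upper end: 1 × 26 × 20 = 520 euros per participant

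Under these assumptions the cost difference moves by 260 to 520 euros in the direction of the difference in informal care, and net benefit moves by the same amount the opposite way.

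**The case against.** The strongest reply is that this is only a matter of labelling. The items are listed openly, so a reader can see what the total contains. Table 2 says who gives the care, not which costing perspective it belongs to, and puts formal and informal care in one row. The Background mentions the burden on formal and informal care together, and the Discussion sentence is general prose, not a costing definition. The authors chose to collect informal care and may simply use the word healthcare broadly.

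Part of this stands. The boundary of a healthcare perspective is a costing convention that the article does not spell out, so changing the label is as consistent a repair as removing the item. But the article offers no broad definition, and its own distinction between formal care and care by relatives or volunteers points the other way. Nor can the full protocol or an analysis plan be expected to settle it as omitted detail: the perspective and the item list are both fixed in the article, and they disagree.

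Three stronger readings are tempting but not supported:

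- **That the error runs to thousands of euros.** A reader might price all of a participant's informal care. At an assumed 2 to 10 hours per week this gives 2 × 26 × 10 = 520 to 10 × 26 × 20 = 5,200 euros. That is a total per participant. It cancels from the cost difference unless the arms differ, so it does not measure bias.
- **That informal care is large and skewed here, or would reverse the sign of the result.** Nothing in the article shows this.
- **That the total fits no perspective because other societal costs are left out.** The list is worded as what costs will include, in a condensed article, and no omitted item of importance for patients aged 65 or over in inpatient rehabilitation can be identified from it.

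**Conclusion.** The inconsistency is real and internal to the article. Followed as written, the plan yields a cost difference and a net benefit that are not the healthcare-perspective quantities named in the objective. Each is off by the full between-arm difference in informal-care cost.

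How much that is, and in which direction, cannot be derived from the article. The 260 to 520 euros per participant rests wholly on an assumed 1 hour per week and an assumed 10 to 20 euros per hour. It shows scale and is not an estimate of bias.

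The reach is limited to the secondary economic objective. The POMA and FES-I analyses and the sample size are untouched. A correction is still worth making, because cost-effectiveness is part of the trial's stated aim and the repair is nearly free.

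**What to change.** Settle the point before costs are compared by arm, so that the perspective is not chosen after the results are seen. Either of two repairs is consistent:

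1. **Keep the healthcare perspective.** Exclude informal care from the base-case healthcare cost. Under Data analyses, add a sensitivity analysis, labelled as a wider perspective, in which informal care is included.
2. **Keep informal care in the base case.** Restate the perspective under Secondary objectives and Economic evaluation so that it matches the items counted, and rename the cost contrast to fit. Add a sensitivity analysis without informal care.

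Either way, readers see the result with and without the item. The cost is a sentence or two of text and one extra analysis. Informal care is already due to be recorded at baseline and both follow-ups, so no new data collection is needed. The article does not say in what unit the questionnaire records it, so the repair should not depend on reporting hours.

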### Sample size

This study tests the null hypothesis that there is no difference in POMA score between the intervention and control group at discharge from GR. The criterion for significance (alpha) was set at 0.050. The test is 2-tailed, which means that an effect in either direction will be interpreted. With a sample size of 40 in both groups, the study will have power of 80% to yield a statistically significant result. Based on our previous research, the minimal clinical relevant difference (mean difference of the POMA at discharge measurement) was set at -3.8, with the common within-group standard deviation at 6.0. The corresponding means are 17.0 vs. 20.8. This effect was selected as the smallest effect that would be important to detect, in the sense that any smaller effect would not be of clinical or substantive significance. It is also assumed that this effect size is reasonable, in the sense that an effect of this magnitude could be anticipated in this field of research.

Compensation for design effect and possible loss to follow-up was taken into account in the choice of sample size. For the design effect (cluster randomisation), the intraclass correlation coefficient (ICC) for the outcome measure POMA is expected to be 0.05 because of clustering of data and because there may be inequality of the numbers within clusters. For the possible loss to follow-up, specifically death in the 3-month rehabilitation phase is not expected be ≥10%. Instead of the 40 patients calculated with the power analysis, we will include 75 patients per group.

As 11 post-acute GR units were interested in participating, we decided to include one additional intervention post-acute GR unit, in case of unsuspected drop-out of one intervention location. Thus, we aim to include a total of 165 participants.

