**Methods/design:**

This multicentre cluster randomised controlled trial will be conducted among older patients with hip fracture and fear of falling who are admitted to a multidisciplinary inpatient geriatric rehabilitation programme in eleven post-acute geriatric rehabilitation units. Fifteen participants will be recruited from each site. Recruitment sites will be allocated by computer randomisation to either the control group, receiving usual care, or to the intervention group receiving the FIT-HIP intervention in addition to usual care. The FIT-HIP intervention is conducted by physiotherapists and will be embedded in usual care. It consists of various elements of cognitive behavioural therapy, including guided exposure to feared activities (that are avoided by the participants). Participants and outcome assessors are blinded to group allocation. Follow-up measurements will be performed at 3 and 6 months after discharge from geriatric rehabilitation. (Cost)-effectiveness and feasibility of the intervention will be evaluated. Primary outcome measures are fear of falling and mobility.

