### Primary objective

In hip fracture patients admitted to multidisciplinary inpatient GR, to compare the effect of the FIT-HIP intervention with usual care in GR, with respect to reducing fear of falling (measured with the Falls Efficacy Scale-International) and improving gait and balance (measured with the Performance-Oriented Mobility Assessment).

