### Effect evaluation

#### Primary outcome

1. Mean difference in the Tinetti Performance Oriented Mobility Assessment (POMA) score [32, 33] at discharge from GR (or at a maximum of 3 months after admittance to GR), compared between FIT-HIP intervention and usual care. The POMA is a measure of mobility function (gait and balance).

2. Mean difference in the Falls Efficacy Scale International (FES-I) score [34–36] at discharge from GR (or at a maximum of 3 months after admittance to GR), compared between FIT-HIP intervention and usual care. The FES-I is a measure of fear of falling.

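### Two primary outcomes, one POMA-only sample size and no success rule: the 5% error rate and the 80% power cannot both be claimed for the two-outcome trial, and no power is shown for FES-I

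*Protocol article*

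**What the plan says.** Two outcomes are given equal primary standing, in three places:

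- Abstract, Methods/design: "Primary outcome measures are fear of falling and mobility".
- Primary objective: the comparison is made "with respect to reducing fear of falling (measured with the Falls Efficacy Scale-International) and improving gait and balance", the latter measured with POMA.
- Primary outcome: item 1 is "Mean difference in the Tinetti Performance Oriented Mobility Assessment (POMA) score" and item 2 is "Mean difference in the Falls Efficacy Scale International (FES-I) score", both at discharge from geriatric rehabilitation (or at most 3 months after admission).

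Sample size names a single hypothesis: "This study tests the null hypothesis that there is no difference in POMA score between the intervention and control group at discharge from GR". It adds that "The criterion for significance (alpha) was set at 0.050", two-tailed. The difference (3.8), SD (6.0), ICC (0.05) and power (80%) are all for POMA. None of these is given for FES-I.

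Data analyses gives one level for the analyses: "the level of significance will be set at" p < 0.05. No section contains an alpha split, a testing order, or a statement that success needs both outcomes or only one.

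**The concern.** The single hypothesis in Sample size does not match the two outcomes listed as primary, so a reader cannot tell which result decides the trial. A split result is plausible here. The intervention acts directly on fear of falling, and the Abstract and Background expect physical function to improve as a consequence. FES-I could therefore move while POMA does not, and the text gives no way to judge that case.

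Two things are at stake. If a significant result on one scale is enough, the chance of a false positive claim exceeds the stated 5%. If both are needed, the stated 80% overstates the chance of success unless FES-I has power close to 100%. The missing rule also cannot credibly be supplied once results by arm are known.

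**Working it through.** **Inputs from the article.** POMA means 17.0 vs 20.8, so difference 3.8; SD 6.0; two-sided alpha 0.05; power 80%; 40 per group before inflation; ICC 0.05; loss below 10%; 75 per group after inflation (all Sample size). At most 15 participants per unit, six intervention and five control units (Randomisation), so 90 vs 75 as recruited.

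**Assumptions, not in the article.** The correlation r between the two test statistics (range 0 to 0.9) and 80% power for FES-I alone.

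**Step 1. Reproduce the POMA figure.**
- n per group = 2 × (1.960 + 0.842)² × 6.0² / 3.8² = 39.1, rounded up to 40.
- A t-test with 40 per group has 79.9% power.
- Design effect = 1 + (15 − 1) × 0.05 = 1.70, and 40 × 1.70 = 68.
- Allowing 10% loss: 68 / 0.9 = 75.6, or 68 × 1.1 = 74.8. Both agree with the planned 75.

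On its own inputs the POMA calculation is sound.

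**Step 2. Success if either outcome is significant at 0.05.** With r = 0 the family-wise error is 1 − 0.95² = 0.0975. For r > 0 it is 1 − P(|Z₁| < 1.96 and |Z₂| < 1.96) under a bivariate normal distribution.

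**Step 3. Success only if both are significant at 0.05.** The error cannot exceed 5%. If each outcome has 80% power, the expected value of each test statistic is 1.960 + 0.842 = 2.80, and joint power is P(Z₁ > 1.96 and Z₂ > 1.96). At r = 0 this is 0.80² = 0.64.

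| r | Either: family-wise error | Either: chance of at least one success, 80% power each | Both: joint power, 80% power each |
|---|---|---|---|
| 0 | 9.75% | 96% | 64% |
| 0.5 | 9.1% | 91% | 69% |
| 0.7 | 8.3% | 89% | 71% |
| 0.9 | 7.0% | 85% | 75% |

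**Step 4. Cost to POMA of an equal alpha split (0.025 each).** Effective size = recruited × 0.9 / 1.70. Power is from the noncentral t distribution with d = 3.8/6.0.

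| Recruited | Effective size | Power at 0.05 | Power at 0.025 |
|---|---|---|---|
| 75 vs 75 | 39.7 vs 39.7 | 79.6% | 70.4% |
| 90 vs 75 | 47.6 vs 39.7 | 83.0% | 74.6% |

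The uninflated 40 vs 40 gives 70.7% at 0.025, so the planned 75 per group has about 70–71%. To restore 80% at 0.025, n = 2 × (2.241 + 0.842)² × 6.0² / 3.8² = 47.4, rounded up to 48. Inflated, 48 × 1.70 / 0.9 is about 91 per group.

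Step 4 handles clustering through the design effect alone, as the article does. It makes no further allowance for the small number of units.

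**The case against.** A reader might infer that neither the 5% nor the 80% applies to this trial. The documents do not support that. The two failures belong to mutually exclusive rules. Under an either-outcome rule the 5% fails, but 80% is a floor for at least one success. Under a both-required rule the 80% fails, but the error stays at or below 5%. For POMA alone, the only claim to which Sample size attaches these figures, both reproduce.

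A reader might also infer that the article adopts an either-outcome rule. It does not state one. The primary objective joins the outcomes with a conjunction, and the Background and Discussion describe a chain from reduced fear to better function. That is no decision rule, but it means the either-outcome reading is the least favourable one rather than the stated plan. Describing the error as nearly double the nominal level suits low to moderate correlation and weakens to 7.0% at 0.9.

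This is also a condensed article with no analysis plan shown. Multiplicity handling and FES-I power inputs may stand elsewhere, and their absence alone would be no finding. What stands is the mismatch in the printed text: two outcomes are listed as primary, one hypothesis is said to be tested, and 0.05 is fixed without qualification.

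Finally, the extra intervention unit softens the cost of an alpha split (74.6% rather than 70.4%), provided that unit does not drop out. And POMA-first is not the only legitimate rule, because FES-I is the direct target of the intervention.

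**Conclusion.** The point holds in this form: without a success rule, the 5% error rate and the 80% power cannot both be claimed for the two-outcome trial, and no power is shown for FES-I.

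The error exceeds 5% only if either outcome can carry the claim. The power shortfall arises only if both are required, and its stated size depends on FES-I having 80% power by itself. True joint power is unknown, because the article gives no FES-I effect size, SD or ICC. The correlation range is likewise an assumption. The POMA calculation itself is not in question.

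**What to change.** Before unblinded data are seen, fix one rule and state it in the article or the analysis plan.

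**Default.** Test POMA at two-sided 0.05. Test FES-I confirmatorily at 0.05 only if POMA is significant; otherwise report FES-I with its confidence interval as supportive. This matches Sample size, holds the family-wise error at 5%, and leaves POMA power and recruitment unchanged. The wording change is small, but the scientific cost is not: if POMA is null, FES-I cannot carry a confirmatory claim, even though it is half of the primary objective and the direct target of the intervention.

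**Alternatives.** The choice belongs to the investigators, but each alternative needs the power restated.
- *Both required:* give the FES-I effect size, SD and ICC, and report joint power. If the outcomes are independent, 80% joint power needs about 89.4% for each (0.894² = 0.80). For POMA that is 52 per group before inflation, or 52 × 1.70 / 0.9, about 98 after.
- *Alpha split, for example Holm:* at 0.025, POMA power is about 70–71% with 75 per group or about 75% with 90 vs 75. Under Holm these are lower bounds, because POMA is tested at 0.05 once FES-I has succeeded at 0.025.

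Whichever rule is chosen, Sample size should say that the 80% refers to POMA alone.

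### The step from 40 to 75 per group allows for design effect and loss but not for having only 10 or 11 randomised units; at two-sided 0.05 power is about 77-79% (6 vs 5 units) or 72-74% (5 vs 5), not 80%

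*Protocol article*

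**What the plan says.** All of the following is in the Sample size section of the protocol article unless noted.

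- Test: "The criterion for significance (alpha) was set at 0.050" and "The test is 2-tailed, which means that an effect in either direction will be interpreted".
- Effect and spread: the "mean difference of the POMA at discharge measurement) was set at -3.8", "with the common within-group standard deviation at 6.0".
- Starting point: "With a sample size of 40 in both groups, the study will have power of 80% to yield a statistically significant result".
- Clustering: "the intraclass correlation coefficient (ICC) for the outcome measure POMA is expected to be 0.05", and the reason given is "because of clustering of data and because there may be inequality of the numbers within clusters".
- Loss: death during the three-month rehabilitation phase is expected to stay below 10%.
- Result: "Instead of the 40 patients calculated with the power analysis, we will include 75 patients per group". A sixth intervention unit is then added as cover in case one intervention unit drops out, for a total of 165.

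The Randomisation section fixes six intervention and five control units with at most 15 participants each, so 75 per group is five units of 15. The Data analyses section plans multilevel models for continuous outcomes. Design effect and loss are the only two adjustments named.

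**The concern.** Treatment is allocated by unit, so the arm effect is judged against variation between units. Ten or eleven units leave 8 or 9 degrees of freedom for that variation. The two-sided 5% critical value is then 2.31 or 2.26, against about 1.98 with patient-level degrees of freedom. A design effect enlarges the variance but leaves the reference distribution unchanged, so a sample inflated by it alone falls short when there are few units.

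At stake is how a null POMA result is read. The protocol calls 3.8 points the smallest effect worth detecting. If the chance of missing it is larger than 20%, a non-significant result is weaker evidence against such an effect than the stated power suggests.

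A second, smaller fault is the treatment of unequal unit size as part of the reason for the ICC value. The ICC is a ratio of variances and does not contain variation in unit size, which enters the design effect as a separate term.

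**Working it through.** **Inputs.** Difference 3.8, SD 6.0, two-sided alpha 0.05 and ICC 0.05 (Sample size); 15 per unit and 6 vs 5 units (Randomisation); loss from 0% to 10% (Sample size, with 10% as its upper bound). SD 6.0 is read as the total SD within an arm.

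**1. The protocol's own figures.**
- Without clustering, SE = 6.0 × √(2/40) = 1.342 and 3.8/1.342 = 2.83. Power is 79.9% with a t-test on 78 df, so 40 per group reproduces.
- Design effect = 1 + (15 − 1) × 0.05 = 1.70. Then 40 × 1.70 = 68 and 68/0.9 = 75.6 (or 68 × 1.1 = 74.8), so 75 reproduces.

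**2. Power with unit-level degrees of freedom.** With m analysed per unit and k1, k2 units:

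DE = 1 + (m − 1) × 0.05; SE = 6.0 × √[DE × (1/(k1·m) + 1/(k2·m))]; noncentrality = 3.8/SE; df = k1 + k2 − 2.

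For example, for 5 vs 5 with 10% loss, m = 13.5 and DE = 1.625, so SE = √(36 × 1.625 × 2/67.5) = 1.317 and the noncentrality is 3.8/1.317 = 2.89.

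| Units | Loss | m | DE | SE | Noncentrality | df | Power | Power, patient-level df |
|---|---|---|---|---|---|---|---|---|
| 6 vs 5 | 0% | 15 | 1.70 | 1.223 | 3.11 | 9 | 78.9% | 87.0% |
| 6 vs 5 | 10% | 13.5 | 1.625 | 1.261 | 3.01 | 9 | 76.5% | 85.0% |
| 5 vs 5 | 0% | 15 | 1.70 | 1.277 | 2.97 | 8 | 74.1% | 84.0% |
| 5 vs 5 | 10% | 13.5 | 1.625 | 1.317 | 2.89 | 8 | 71.6% | 81.7% |

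Simulating unit means (200,000 runs each) gave 76.6% for 6 vs 5 and 71.5% for 5 vs 5 with 10% loss. The last column shows that the reference distribution causes the shortfall, since the SE is the same in both power columns.

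**3. Detectable difference at 80% power with 10% loss.** It is 4.0 points (6 vs 5) or 4.2 points (5 vs 5), against the planned 3.8.

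**4. An uncorrected z test from the multilevel model (simulated, 10% loss).** With REML, power is 84.0% (6 vs 5) and 80.7% (5 vs 5), with type I error of 6.7% and 6.9%. With maximum likelihood, type I error is 8.6% and 8.9%. The 80% is therefore reached only by exceeding the stated 5%.

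**5. Sensitivity to the ICC (10% loss).** The values other than 0.05 are assumptions.

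| ICC | 5 vs 5 | 6 vs 5 |
|---|---|---|
| 0.02 | 82% | 86% |
| 0.05 | 72% | 77% |
| 0.10 | 58% | 63% |

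**The case against.** Nothing in the section is miscalculated: both 40 and 75 reproduce. The 80% is printed beside 40 per group, and no power is printed for 75 or 165. This stands. That 80% is meant to carry over is an inference, though it is the only evident purpose of the inflation.

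The degrees-of-freedom method may be set in an analysis plan that is not shown. That is fair as regards the analysis, and the absence of a named correction is not held against the protocol. It does not rescue the power figure. A corrected test gives the powers in the working, and an uncorrected one breaks the stated alpha.

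Baseline adjustment could recover the loss. If a baseline correlation of 0.3 is assumed and the variance is multiplied by 1 − 0.3² = 0.91 at both levels, 6 vs 5 reaches about 80% with 10% loss. At 0.5 it reaches about 87%, and 5 vs 5 about 83%. The protocol gives no such correlation and does not count on one.

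Three stronger readings are tempting and are not supported:

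- *The trial as randomised has only about 72% power.* The randomised design is 6 vs 5 units. The figure near 72% needs both the loss of an intervention unit and the full 10% loss, which the protocol gives as a level it does not expect to reach.
- *The sponsor expects to lose a unit.* The text describes cover for an unforeseen event. The sixth unit also adds 15 patients above the 75 required in that arm.
- *Unequal unit size removes much more power.* With a cap of 15 and a mean of 13.5 analysed, the coefficient of variation of unit size cannot exceed √(1.5/13.5) = 0.33, which would need one unit empty among ten. The wording about the ICC is wrong, but the documents support no large further loss.

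**Conclusion.** The point holds, at moderate size. At the protocol's own difference, SD, ICC and two-sided alpha of 0.05, every scenario from 0% to 10% loss is below 80%. For the 11 randomised units the shortfall is about 1 to 3.5 percentage points. For 5 vs 5 it is about 6 to 8 points, so the chance of missing a true 3.8-point difference is about 26-28% where 20% was planned.

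This rests on equal unit sizes, SD 6.0 as the total SD, no baseline adjustment, and a test with degrees of freedom equal to units minus two. It depends strongly on the ICC: at an assumed 0.02 both designs exceed 80%, and at an assumed 0.10 both fall to about 60%. The fault lies in the reference distribution behind the stated power, and it does not show that the trial is too small to run.

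**What to change.** Keep 165 participants and the 6 vs 5 allocation, and revise the Sample size section as follows.

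1. State power as about 77-79% with 11 units and about 72-74% with 10 units (10% to 0% loss), computed with unit-level degrees of freedom.
2. Add a short table with ICC values on both sides of 0.05, such as 0.02 and 0.10, labelled as assumptions.
3. Remove unequal unit size from the justification of the ICC. If it is to be allowed for, put it in the design effect with a stated coefficient of variation that is compatible with the cap of 15.
4. If the primary analysis adjusts for baseline POMA, state power for that analysis with its assumed correlation.

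The cost is a slightly less favourable published figure. No patients, units or visits are added.
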